### Ethical Considerations

Ethics approval was obtained from the University of Western Australia (2018/RA/1/2301/4) and the PNGIMR Institutional Review Board (1809) in 2018 and the PNG Medical Research Advisory Committee (18.20) in 2019. The study has been registered as a clinical trial in PNG under the National Department of Health Pharmaceutical Standards Branch (CT04 MRAC18.20) and has also been registered with the Australian New Zealand Trials Registry (ACTRN12620001369910).

Before and throughout the study, clinic and field staff conducted awareness and information sessions within communities in and near Goroka, the Goroka Provincial Hospital prenatal clinic, and rural health centers. Formal letters and information about the study were also sent to the Eastern Highlands Provincial Health Authority and senior management of Goroka Provincial Hospital, from whom approval was obtained before study commencement.

Healthy, pregnant women late in the third trimester were approached in the prenatal clinic at Goroka Provincial Hospital or in their local communities by a study health extension officer (HEO) or nurse. The women were given information about the study and given the opportunity to discuss participation with their families. Women who assented to be part of the study were approached within 72 hours of giving birth at the Goroka Provincial Hospital labor ward or postnatal clinic. Their consent was confirmed, and if all inclusion criteria were met, the infant was enrolled in the study. Written parental consent was obtained before enrollment.

The study was conducted according to the Declaration of Helsinki, the International Conference on Harmonisation Good Clinical Practice, and local ethical guidelines. All participants were assigned a unique study number that was detached from their personal information. Personal data were accessible only to key investigators and were not linked with samples for processing. All data were therefore anonymized. Hard copies of participant information containing identifiable details were securely stored in locked offices. At the end of March 2023, due to higher-than-anticipated loss to follow-up because study infants’ families left the study area, largely owing to the COVID-19 pandemic, ethics approval was obtained to recruit additional participants.

### Inclusion and Exclusion Criteria

The inclusion and exclusion criteria are presented in Textbox 1.

If the mother of an already enrolled child developed fever or abdominal tenderness within 2 days of giving birth, the child remained eligible to stay in the study as long as the child was clinically well.

Infants were deemed eligible to participate and to not have any congenital abnormalities based on clinical assessments conducted routinely by hospital pediatricians on newborns delivered at Goroka Provincial Hospital and by a study HEO.

Inclusion and exclusion criteria.
**Inclusion criteria**
Infant birth weight ≥1.5 kgInfant aged <72 hInfant feeding orally within the first 72 h of lifeMother and infant residing within 60-min driving distance from the Papua New Guinea Institute of Medical Research in GorokaFamily intending to remain in the study area for at least 6 mo (duration of the study)Parental written informed consent obtained
**Exclusion criteria**
Mother HIV positive or of unknown statusMother with foul-smelling amniotic fluidHeavy meconium staining of amniotic fluidMother with fever (>38 °C) within −2 or +2 d of deliveryMother with abdominal tenderness within 2 d of deliveryParents unable or unwilling to provide consentInfant receiving antibiotics between birth and screening (within the first 72 h of life)Infant with signs or symptoms of suspected infection at the time of screeningInfant with a major congenital abnormalityInfant with an Apgar score of <8

### Study Interventions

The synbiotic products and placebo were manufactured by DuPont Nutrition and Biosciences, now part of International Flavors and Fragrances Inc (IFF), and supplied in September 2020 before the study commenced, in quantities sufficient for the full target cohort. An additional 10% was provided to allow for repeat doses (eg, in cases of vomiting after administration) and for any additional enrollments to account for anticipated loss to follow-up. A full replacement batch was supplied by IFF in November 2022 due to the expiry of the initial batch before recruitment had been completed. The intervention products were shipped at room temperature and stored at the PNGIMR at 4 °C until use.

Two probiotic supplements—single-strain *L plantarum* and *B longum* subspecies *infantis—* compared to placebo were used in this study. These 2 probiotic supplements were prepared as synbiotics and supplied, as with the placebo, lyophilized in glass vials. Each vial contained a single dose of one of the following: (1) *L plantarum* (ATCC 202195; 1.0×10^9^ colony-forming units) + 150 mg of fructo-oligosaccharide, with 100 mg potato maltodextrin as excipient (matching the preparation used in the Indian trial [23]); (2) *B longum* subspecies * infantis* (Bi-26; at least 1×10^9^ colony-forming units) + 1.2 g of the human milk oligosaccharide 2′-fucosyllactose, with 100 mg potato maltodextrin as excipient; or (3) placebo (100 mg potato maltodextrin).

### Randomization

A computer-generated randomization list was maintained by DuPont Nutrition and Biosciences (now part of IFF) such that the research investigators, research and laboratory staff, and study participants remained blinded to the intervention arms. A single randomization code (sequential numbers 1-215) was assigned to each carton of intervention product, which contained 7 vials—one for each day of administration (d 1-d 7)—and was allocated consecutively to each enrolled child. Each vial was labeled with the specific trial randomization code and the corresponding day of administration. After the expiry of the initial batch, the replacement intervention products, also sequentially numbered, were used to continue enrollment beyond participant 215. The same blinding randomization procedures were followed to ensure allocation concealment and consistency throughout the trial.

### Intervention Administration, Vaccination, and Follow-Up

The schedule of synbiotic administration, routine infant vaccinations, and specimen collection throughout the study is shown in Figure 1. Just before administration, a single vial of intervention product corresponding to the appropriate day of administration (d 1-d 7) was diluted by adding 3 mL of either breast milk or sterile water directly to the vial, followed by inverting 5 times to mix and resuspend the contents. The resulting suspension was administered to the infant in oral drops using a Pasteur pipette, similar to the method used for oral polio vaccine. Before administration, infants were breastfed and burped. The intervention was administered by PNGIMR study staff (HEO or study nurse). When the intervention was administered at participants’ homes, the product vials were transported in small portable coolers with ice packs. The infant was monitored for 30 minutes after receiving the intervention. In cases of vomiting, the dose was repeated an hour later. A missed dose was defined as any scheduled daily dose (d 1-d 7) not administered on the same day, regardless of the reason, including participant unavailability, vomiting without readministration, or logistical barriers to follow-up. During the observation period, infants were taken to the PNGIMR clinic for examination and treatment (if the intervention had been administered elsewhere) and referred to Goroka Provincial Hospital when necessary. Obstetrics information and baseline characteristics were obtained on the day of enrollment. At each follow-up visit, the infant’s health was reviewed before any intervention administration, vaccination, or specimen collection. Weight and length measurements were recorded, and information on feeding practices was also collected at each visit.

**Figure 1 figure1:**
[figure not shown]
Schedule of synbiotic or placebo administration, routine infant vaccinations, and specimen collection throughout the study.

Routine childhood vaccines, including the pentavalent vaccine (DTwP, hepatitis B, and Hib), PCV13, and oral polio vaccine (Figure 1) were obtained through the Eastern Highlands Provincial Health supply chain and administered by study HEOs or nurses at ages 1, 2, and 3 months as per PNG’s expanded program on immunization. Inactivated polio vaccine was also administered at age 3 months, and the first dose of the measles vaccine was administered at the completion of the study (6 mo). Birth doses of bacillus Calmette-Guérin (BCG) and hepatitis B vaccines were generally administered by hospital staff. In instances where this did not occur, study HEOs and nurses administered them at the time of enrollment. All vaccinations administered were recorded in the child’s health book held by the parent or guardian.

Follow-up visits were conducted at either the PNGIMR clinic or at the participant’s home. When blood collection was scheduled (at enrollment, on the day of the last intervention administration, and at ages 1 and 4 mo), participants were brought to the PNGIMR clinic for review and sample collection. All other follow-up visits were carried out by the clinical and field staff at the participants’ place of residence. Up to 3 home visit attempts were made for each participant follow-up before a child was withdrawn from the study after being deemed unlocatable. Children were also withdrawn from the study if information had been received that the family had permanently moved out of the study area, if parents or guardians withdrew consent, if a protocol violation occurred, or if the investigators determined that continued participation could adversely affect the child’s health.

### Morbidity Surveillance

All serious adverse events (SAEs) that occurred during the study period were recorded. The variability in diagnostic terms and a lack of gold standard case definitions for neonatal sepsis make it difficult to compare incidence, severity, etiology, or disease outcomes across studies and settings. Therefore, instead of sepsis, we examined “severe infection” as a clinical outcome, acknowledging that many infants will not manifest overt signs of sepsis and using the qualifier “severe” to indicate that localized infections without systemic features (eg, skin pustules) will be excluded. Severe clinical infection was defined as the presence of at least one of the following signs or symptoms to align with a similar study of synbiotics in Bangladesh [31]: (1) poor feeding (not sucking effectively or not sucking at all, as directly observed), (2) lethargy (movement only when stimulated or not moving at all, as directly observed), (3) convulsions (observed or strongly suspected by the clinician based on caregiver or community health worker report), (4) severe chest in-drawing (observed), (5) fever (axillary temperature of ≥38 °C), and (6) hypothermia (axillary temperature of <35.5 °C). In addition, any subsequent positive sterile site cultures or hospitalization with intention to treat with antibiotics for at least 5 days was considered indicative of severe clinical infection.

Throughout the study, the pediatric ward at Goroka Provincial Hospital was monitored daily for possible admissions of study infants. For any participant admitted, clinical information on health status, reason for admission, treatment, and discharge outcomes was recorded. In addition, parents or guardians were encouraged to bring their infants to the PNGIMR clinic for any illness experienced to enable SAEs to be recorded during this period. If clinically indicated, specimens were collected to aid in health assessment and diagnosis. Clinical samples included small volumes of blood (approximately 2 ml), stool, and a nasopharyngeal swab. Samples were processed at the PNGIMR laboratory, and the results were returned to the study clinicians for dissemination to the participant’s parent or guardian.

If a child was unwell during a scheduled study visit, routine procedures such as intervention administration and sample collection were still conducted unless contraindicated.

In addition, as in previous clinical trial studies led by the PNGIMR, study children’s family members who became unwell were also seen at the PNGIMR clinic as needed during the 6-month participation period.

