**Methods:**

Following ethics approvals in 2018 and 2019, and receipt of the synbiotic preparations in September 2020, healthy neonates (<72 h old; n=244) were recruited between October 2020 and June 2023 and randomly assigned in a double-blind manner (1:1:1) to receive an oral preparation containing *Lactiplantibacillus plantarum*, *Bifidobacterium longum* subspecies *infantis*, or placebo for 7 consecutive days. Follow-up continued for 6 months, with rectal swabs, stool, blood, saliva, and nasopharyngeal swabs collected before the intervention; on day 7; at age 2 weeks; and at ages 1, 3, 4, and 6 months. Ongoing analyses will assess probiotic gut colonization, bacterial nasopharyngeal carriage, and antibody responses to routine childhood vaccines (*Hemophilus influenzae* type b; hepatitis B; 13-valent pneumococcal conjugate vaccine; and diphtheria, tetanus, and whole-cell pertussis) as well as hospitalization and infection rates among the intervention groups compared to the placebo group.

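### As written, one axillary temperature of 38 °C or more counts as severe clinical infection, with no age window and no provision for fever after the vaccines given at 1, 2 and 3 months

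*Protocol article*

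**What the plan says.** All references are to the protocol article.

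- **Case rule (Morbidity Surveillance).** "Severe clinical infection was defined as the presence of at least one of the following signs or symptoms". Six signs follow, and the fever item is "5) fever (axillary temperature of ≥38 °C". It asks for no second sign, repeat reading, duration or attribution to infection. A positive sterile-site culture, or an admission with at least 5 days of antibiotics intended, also qualifies.
- **Exclusion.** The only one stated is that "localized infections without systemic features (eg, skin pustules) will be excluded".
- **Rationale.** The outcome replaces sepsis because of the "lack of gold standard case definitions for neonatal sepsis", and it is aligned with a synbiotic study in Bangladesh. No age range is attached.
- **Surveillance.** "All serious adverse events (SAEs) that occurred during the study period were recorded", and the Abstract says "Follow-up continued for 6 months". Outside scheduled visits, "parents or guardians were encouraged to bring their infants to the PNGIMR clinic for any illness experienced".
- **Vaccines (Intervention Administration, Vaccination, and Follow-Up).** Pentavalent vaccine (including whole-cell pertussis), PCV13 and oral polio vaccine were "administered by study HEOs or nurses at ages 1, 2, and 3 months as per PNG’s expanded program on immunization". Each infant's health was reviewed before the vaccine was given.
- **Use.** The Abstract promises a comparison of infection rates with placebo, and Study Rationale and Objectives names infection rates among the secondary and exploratory aims.

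**The concern.** A fever caused by a vaccine is not an infection. The rule cannot tell the two apart, and the schedule creates up to three occasions per infant on which they can be confused. An infant brought to the clinic the day after a dose with 38.2 °C and no other sign meets the definition, and nothing in the article removes that episode.

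Two uses of the outcome would suffer. First, false cases shared by all arms dilute a true difference from placebo. Second, the pilot's overall objective is to inform the design of a definitive trial, including its clinical end points. A base rate that contains vaccine reactions would mislead that design even if the reactions were perfectly balanced.

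**Working it through.** The article states no rate, power or sample size for severe infection, so there is no figure of its own to reproduce. The check has a textual part and an illustration.

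**Text.** Fever alone suffices; the one exclusion concerns localized infection; no age window is written; the vaccine doses fall inside follow-up. Together these make a recorded isolated post-vaccine fever a case.

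**Illustration.** All risks here are assumptions. Let *p* be the true risk of severe infection and *f* the share of infants with at least one *recorded* isolated post-vaccine fever, equal across arms and independent of infection. Then

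observed risk = *p* + (1 − *p*)*f*

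Example: 0.10 + 0.90 × 0.05 = 0.145 on placebo and 0.05 + 0.95 × 0.05 = 0.0975 on active; 0.0975 / 0.145 = 0.67.

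| True risks | *f* | Observed risks | Risk ratio | Vaccine-fever-only share of placebo cases |
|---|---|---|---|---|
| 10% v 5% | 0 | 10% v 5% | 0.50 | 0% |
| | 5% | 14.5% v 9.75% | 0.67 | 31% |
| | 10% | 19% v 14.5% | 0.76 | 47% |
| | 20% | 28% v 24% | 0.86 | 64% |
| 20% v 10% | 0 | 20% v 10% | 0.50 | 0% |
| | 5% | 24% v 14.5% | 0.60 | 17% |
| | 10% | 28% v 19% | 0.68 | 29% |
| | 20% | 36% v 28% | 0.78 | 44% |

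The last column is (observed − *p*) / observed. The risk difference suffers less than the ratio: it is multiplied by (1 − *f*), so 5 points becomes 4.75, 4.5 or 4.0.

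To relate *f* to doses: if each of three doses independently led to a recorded isolated fever with probability *q*, then *f* = 1 − (1 − *q*)³. That gives 5.9%, 14.3% and 27.1% for *q* = 2%, 5% and 10%.

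**Effect on planning the larger trial.** Take 80% power, two-sided 5%, *n* per arm = 7.849 × [*p*₀(1 − *p*₀) + *p*₁(1 − *p*₁)] / (*p*₀ − *p*₁)².

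- Halving a true 10%: 7.849 × (0.0900 + 0.0475) / 0.05² = 432.
- Halving an observed 19% (*f* = 10%), taken as if it were all infection: 7.849 × (0.1539 + 0.0860) / 0.095² = 209.

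A planner who took the diluted pilot rate at face value would choose roughly half the number needed.

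**Exposure.** Table 1 shows 226 infants at 1 month and 196 at 3 months. It has no 2-month column, and the 4-month visit is not a vaccine visit.

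**The case against.** Much of the opposing case stands.

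- **Six months is inferred.** The rationale speaks of neonatal sepsis, and the Introduction takes the neonatal period as the first 28 days. If that window was meant, most or all of the scheduled doses fall outside it and the problem largely disappears. The article does not say so, however, and it places the definition under study-long surveillance.
- **Few may be captured.** Health review comes before vaccination, and no temperature check afterwards is described. Recording depends mainly on voluntary clinic attendance, with ward monitoring for admissions. A reader might infer that vaccine fevers have in fact been scored as infections in number; the article does not show that.
- **The frequency is not in the article.** That vaccination can be followed by fever is general clinical knowledge. How often it was recorded here is unknown, so every *f* above is assumed.
- **The outcome is minor here.** Study Design and Objectives lists hospitalization but not severe infection, Statistical Analyses gives it no analysis of its own, and it does not drive the sample size. With 80 per arm and no vaccine fever at all, power to detect a halving is about 42% from a 20% placebo risk and 22% from 10%. No efficacy conclusion turns on the dilution.
- **The definition was chosen for comparability.** This is a good reason to keep it, but not a reason to report it alone.

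Two stronger readings fail. One is that the rule contradicts its own qualifier: the text excludes localized infection without systemic features, not minor illness generally, and fever is a systemic feature. The other is that synbiotics might raise vaccine reactogenicity and so create a false harm signal. The article plans to study vaccine responses, but nothing in it supports that effect, and blinded allocation makes roughly equal misclassification the more natural assumption.

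Leaving detail to a full protocol or analysis plan does not answer the point. The article gives a complete case rule with cut-offs and an exclusion, and that rule, applied as stated, misclassifies.

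**Conclusion.** The point holds in limited form. The written definition counts a recorded, isolated post-vaccine fever as severe clinical infection, and the schedule places three sets of doses inside the period to which, on its face, the definition applies. The likely effects are an inflated infection rate and a comparison pulled toward no difference. On the assumed rates, a true risk ratio of 0.50 would be seen as 0.67 to 0.86 (10% v 5%) or 0.60 to 0.78 (20% v 10%) when *f* runs from 5% to 20%.

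This rests on there being no unstated neonatal window, on some such fevers being recorded, and on equal frequency across arms. The actual size cannot be known from the article. Because severe infection is neither primary nor a listed objective, the matter is moderate. It is worth correcting chiefly because the larger trial will draw on these rates.

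**What to change.** Before unblinding:

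1. State the age window to which the definition applies. If it is neonatal, say so; little else may then be needed.
2. Keep the present definition and report it, for comparability with the Bangladesh study.
3. Report beside it a prespecified second version that does not count an episode when all of these hold: fever is the only qualifying sign; the recorded presentation date falls within a short fixed interval (e.g. 2 days) after a study-administered vaccine dose; there is no positive sterile-site culture; and there is no admission with at least 5 days of antibiotics intended.

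Use the presentation date, because nothing shows that fever onset times were collected. Use the actual dose date rather than the scheduled age, because Protocol Violations reports delayed doses. The Feasibility section already gives dose completion by named arm, so some of the team may know the allocation. If so, people without access to it should fix and apply the rule before any tabulation of infections by arm.

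The cost is one definition line and one date comparison per fever-only episode, provided that dose dates are held in study records as well as in the parent-held health book. The downside is that a true fever-only infection coinciding with vaccination drops out of the second version, which is why both are reported. The change concerns outcome classification only, not care.

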### Specimen Collection

For the secondary and exploratory objectives of the study, a number of biological samples were collected at several time points throughout the study (Figure 1). Rectal swabs and stool samples were collected to assess intestinal colonization by probiotic species. Rectal swabs were collected at enrollment; on the day of the last intervention administration (age 7-10 d); and at ages 2 weeks, 1 month, 3 months, 4 months, and 6 months. For sample collection, the infant was carefully placed face down across the mother’s thighs. A FLOQSwab (Copan Diagnostics) was gently inserted approximately 2 cm into the anal canal, rotated slowly for 10 seconds, then removed and placed into a tube containing eNAT preservation and transport medium (Copan Diagnostics). The swab was broken at the breakpoint, leaving the tip in the tube, which was then sealed and mixed by inverting 10 times. Stool samples were collected in addition to rectal swabs if infants passed stool during the study visit to allow for sensitivity comparisons of probiotic strain detection in rectal swabs versus stool. Stool samples were taken from infants’ diapers using a scoop and placed into stool specimen containers for storage and transportation. Upon arrival at the PNGIMR laboratory, stool samples were transferred to cryovials by laboratory staff. Both rectal swabs and stool samples were then stored at −80 °C.

Nasopharyngeal swabs to assess bacterial carriage and load were collected at ages 2 weeks, 1 month, and 4 months using FLOQSwabs. At each time point, 2 swabs were collected per infant when possible. For each collection, a swab was inserted horizontally into the nostril to collect a superficial mucosal sample from the anterior nares, advancing gently until resistance was met. The swab was then rotated while counting to 5 (or for approximately 3 s) before being removed. One swab was placed in skim milk tryptone glucose glycerol broth (STGGB) for culturing of bacterial pathogens (priority), and the second was stored in PrimeStore molecular transport medium (Thermo Fisher Scientific) for deep sequencing. Both samples were stored at −80 °C.

Venous blood (maximum 2 mL at visits 1 and 2 and maximum 4 mL at visits 9 and 12) and saliva (visits 1, 7, 9, and 12) samples were obtained to assess systemic and mucosal vaccine responses and identify intervention-associated pathways or markers of immune maturation using systems biology approaches. Blood was collected using small 20-gauge butterfly needles and syringe techniques to reduce the risk of vein collapse. A maximum of 2 attempts were made to obtain a blood sample at each visit; if unsuccessful, no further attempts were made. For systems biology studies, we collected up to 2 mL of blood in heparin tubes. These samples were processed at the PNGIMR laboratory within 15 minutes of collection for RNA (transcriptomic analysis), plasma (proteomic and metabolomic analysis), flow (single cell immunophenotyping), and white blood cells (proteomic, metabolomic, and epigenetic analysis), following a protocol established by the Expanded Program on Immunization Consortium [32]. For serology, we collected up to 2 mL of blood in standard serum tubes, and the serum was separated and stored in cryovials by laboratory staff. Blood for serology was prioritized at ages 1 and 4 months over blood for systems biology. Saliva samples were collected from infants, ideally at least 30 minutes after being breastfed, using 4 to 6 surgical eye spears (Defries Industries) placed on the floor of the mouth to absorb saliva from the gums until saturated. The eye spears were then transported in 15 mL Falcon tubes (Corning Incorporated) to the PNGIMR laboratory where they were centrifuged at 10,000 g at 5 °C for 10 minutes. Saliva recovered after centrifugation was transferred to cryovials for storage. If no saliva was obtained after centrifugation, the sample was discarded. All blood products and saliva samples were initially stored at −80 °C at the PNGIMR before being shipped on dry ice to The Kids Research Institute Australia (formerly Telethon Kids Institute) in Perth, Western Australia, Australia.

Mothers were asked to self-collect vaginal swabs shortly after delivery using eNAT FLOQSwabs. These samples were used to collect information on the background prevalence of maternal vaginal carriage of probiotic species, in addition to pathogens associated with neonatal sepsis, such as group B *Streptococcus* and *Escherichia coli*, which may be vertically transmitted to the infant at the time of delivery. The swabs were stored at −80 °C.

Excess expressed breast milk was also collected at each intervention visit (visits 1-7) and stored at −80 °C at the PNGIMR for later analysis of protein (including antibodies) and carbohydrate content.

